## 4. Outcomes

The main outcome that is being evaluated in this pilot study is whether the intended number of participants could be recruited, within the duration of one year. This pilot study also seeks to determine if the intended processes of randomization and the administration of the intended interventions would be successful. In this current pilot study, we acknowledge that selection biases are present, in that we are selecting a cohort of participants that voluntarily seek admission to the inpatient unit. Moreover, the administration of the screening test would also imply that we are selecting specifically for individuals with positive baseline biases only. We are of the opinion that such biases could not be reduced and removed, and we will acknowledge them in our final published study. We will also acknowledge that such biases might affect the overall generalizability of our results. 

### 4.1. Statistical Analyses

For data analysis, an intention to treat analytical approach will be used, to include all participants, including those who withdrew and those who are prematurely discharged from the inpatient unit. Microsoft Excel will be used for the computation of the attention bias scores for each participant for each of the assessment task, in accordance to this formula:(∑T_1_/n_1_) − (∑T_0_/n_0_),
where 

T_1_ refers to the time for probes that replaced the neutral stimulusn_1_ refers to number of trials for probes that replaced the neutral stimulusT_0_ refers to the time for probes that replaced the substance stimulusN_0_ refers to number of trials for probes that replaced the substance stimulus

SPSS Version 24.0 (SPSS Inc., Chicago, IL, USA) will be used for the analysis of the quantitative data. Demographic and clinical information data of the subjects in both groups will be summarized using descriptive statistics, including that of means and standard deviations. Chi-square tests will be used to determine if there are differences in the two groups for each of the demographic or clinical information variables. We plan to run ANOVA (analysis of variance) analysis to examine the differences in the outcome measure (attention bias scores/reaction time) across the time points in the actual definitive trial. P-values less than 5% will be considered statistically significant. 

For the qualitative data obtained by means of the perception questionnaire, the data will be coded using NVivo 12, and a thematic analysis approach will be used in the analysis. 

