## Abstract

**Introduction**: Globally, there is an epidemic of opioid use disorders. Locally, in Singapore, there is an increase in the number of individuals abusing opioids. The advances in experimental psychology have highlighted the need to modify unconscious, automatic biases. These automatic, unconscious biases result in individuals having preferential attention to substance-related cues in their natural environment, thus leading to a slip or relapse back into their underlying addictive disorders. Prior studies have demonstrated not only the presence of robust attentional biases amongst individuals with opioid use disorder, even when maintained on methadone; and the effectiveness of bias modification amongst these individuals. There remains limited evaluation of attention bias modification amongst a treatment-seeking cohort of Asian individuals. The objective of this pilot is to ensure that the methods of the planned definitive randomized trial could be conducted. **Methods and Analysis**: A non-blinded pilot randomized trial will be conducted. A total of 30 participants will be randomized to receive either the conventional application or the newly designed co-designed application. In order to identify these 30 participants, 60 participants will be recruited and screened to determine if they have baseline biases. Participants will be recruited from the inpatient unit at the National Addictions Management Service (NAMS) Singapore. All participants who are enrolled into the trial will complete a baseline assessment task, and a bias modification assessment and modification task daily. They will have to complete a baseline demographic and clinical information questionnaire, as well as a cravings rating scale before and after the intervention daily. Perspectives—that of self-reported experiences—will be sought from the participants following their completion of three intervention tasks. Descriptive statistical analyses will be performed, and chi-square and ANOVA analyses will be performed. Qualitative analyses will be undertaken for the perspectives shared. **Ethics and Dissemination**: Ethical approval has been obtained from the National Healthcare Group’s Domain Specific Research Board (DSRB) (approval number that of 2019/00934). The findings arising from this study will be disseminated by means of conferences and publications.

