## 2. Methods

### 2.1. Study Design and Setting

The study design will be that of a non-blinded randomised controlled trial. Participants will be allocated to receiving either the conventional attention bias modification task, or that of the co-designed task. Simple randomisation will be used. The study will be conducted on the inpatient unit at the National Addictions Management Service, Institute of Mental Health, Singapore. This is a non-blinded randomised trial, as participants who are allocated to both the groups will knowingly be aware of their treatment allocation. It is also not practical for study team members to be blinded, as they are to be responsible for the group allocation, intervention and data collation. 

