### 2.3. Sampling and Recruitment

Convenience sampling will be used in the recruitment of participants over a period of 12 months, at the inpatient unit of the National Addictions Management Service (NAMS), Institute of Mental Health Singapore. The inpatient unit at NAMS offers a 2-week program, in which the first week of the program is focused on the provision of medication-assisted detoxification and the second week of the program is focused on rehabilitation. The unit can have a total of 22 inpatients at any one time. It is also crucial to note that the program is voluntary in nature, which implies that participants are free to leave the ward if they wish to, at any juncture of their inpatient treatment. All participants who have demonstrated interest in the study will be asked to undertake a baseline attention bias assessment task. Only participants who have baseline biases will be recruited into the trial and will be randomly assigned to any of the two groups by means of simple randomisation. Figure 1 provides an overview of the participant flowchart following screening and recruitment.

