**Screening for Eligibility**

Informed consent will be acquired from participants on the last day of their detoxification stay (Day 7), for the purposes of screening, in the presence of an impartial witness. For the screening for the presence of baseline attentional biases, participants are required to undertake an attention bias task on a tablet device. In the assessment task, participants will be shown a fixation cross for 500 milliseconds, followed by a set of images (one related to their substance of use and another neutral image that is similar in complexity). While 50% of these images will be presented for a short stimulus duration of 200 milliseconds, the other 50% of the set of images will be presented for a long stimulus duration of 2000 milliseconds. Following the disappearance of the images, participants are presented with a probe (in the form of an asterisk) for 200 milliseconds. Participants are required to indicate their response, by means of tapping the buttons on the screen, to indicate if the asterisk is presented on the left or right side. If they do not respond, they will be presented with the next trial. In the screening phase, 50% of the trials (100 trials) will involve the presentation of the probe with the substance image, and 50% of the remaining trials will involve the presentation of the probe with the neutral image. The presence of attentional bias will be computed by means of subtracting the reaction time that participants take to respond to probes that replace the neutral image from the reaction time to the probe that replaced the substance image. 

**b.** 

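### Section 4.1 plans an ANOVA of bias scores without naming the Day 7 screening score as a covariate, although adjusting for it would improve precision and guard against chance imbalance (minor)

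*Protocol article*

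**What the plan says.** **The analysis.** Section 4.1 of the protocol article gives the method for the bias outcome: "We plan to run ANOVA (analysis of variance) analysis to examine the differences in the outcome measure", which it then identifies as attention bias scores or reaction time, "across the time points in the actual definitive trial". It names no covariate and does not list the time points. The abstract is broader: "Descriptive statistical analyses will be performed, and chi-square and ANOVA analyses will be performed", with no restriction to the later trial.

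**The screening score.** Section 2.3 says "All participants who have demonstrated interest in the study will be asked to undertake a baseline attention bias assessment task", and only those with a bias go on to be randomised. Under Screening for Eligibility, "participants are required to undertake an attention bias task on a tablet device" on Day 7, before allocation. The abstract counts this among the trial's measurements: "All participants who are enrolled into the trial will complete a baseline assessment task". Section 4.1 foresees "computation of the attention bias scores for each participant for each of the assessment task".

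**Later scores.** Under Experimental Procedure, each day's assessment task follows that day's intervention task. The screening score is therefore the only bias measure free of training.

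**Allocation.** "Simple randomisation will be used" (Section 2.1), and Section 2.5 confirms that no constraint is applied. Section 2.4 plans 15 participants per arm. Section 4 makes recruitment within one year the main outcome.

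**The concern.** A measure of the outcome itself, taken before allocation and held for everyone, is usually the most useful covariate a trial has. Here it exists by design, because it decides entry, and allocation does nothing to balance it between the arms. The stated method does not say that it will be used to adjust the comparison of the two apps.

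Two things are at stake. The first is precision: the part of the later score that the screening score predicts stays in the error term. The second is behaviour after an unlucky allocation: if one arm starts with clearly higher bias, an unadjusted comparison of later scores carries part of that gap into the estimated app effect. Both matter for planning, because Section 2.4 says the pilot is to inform the definitive sample size, and that size depends on whether the variance carried forward is adjusted or unadjusted.

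**Working it through.** **Inputs from the article:** 60 screened, about 50% with bias, 15 per arm (Section 2.4); significance at 5% (Section 4.1), taken as two-sided. The article gives no SD, effect size or correlation.

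**The plan's own figure.** 60 × 0.50 = 30, or 15 per arm, so it reproduces. The earlier study described in the Introduction had 8 of 17 opioid participants without bias; 60 × 9/17 = 31.8, which agrees.

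**Step 1: chance imbalance at screening.** The difference in arm means has SE = SD × √(2/n).
- n = 15 per arm: √(2/15) = 0.365 SD, 95% range ±1.96 × 0.365 = ±0.72 SD. P(|difference| > 0.3 SD) = 41%; P(> 0.5 SD) = 17%.
- n = 50 (illustrative): SE 0.200, range ±0.39 SD, P(> 0.5 SD) = 1.2%.
- n = 100 (illustrative): SE 0.141, range ±0.28 SD.

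**Step 2: variance removed by adjustment.** Assume normal scores with equal SDs, screening scores centred at zero (consistent with 50% positive), entry only above zero, and a correlation ρ with the post-training score before selection. Selection cuts the screening variance to v = 1 − 2/π = 0.363. Among those randomised:
- share of post-training variance explained = ρ²v / (ρ²v + 1 − ρ²)
- share of change-score variance explained = (1 − ρ)²v / ((1 − ρ)²v + 1 − ρ²)

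| ρ before selection | Correlation after selection | Removed from post-training score | Removed from change score |
|---|---|---|---|
| 0.3 | 0.19 | 0.0327/0.9427 = 3.5% | 0.1781/1.0881 = 16.4% |
| 0.5 | 0.33 | 0.0908/0.8408 = 10.8% | 0.0908/0.8408 = 10.8% |
| 0.7 | 0.51 | 0.1781/0.6881 = 25.9% | 0.0327/0.5427 = 6.0% |

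A simulation gave 3.6%, 10.8% and 26.0% for the post-training score and 16.2%, 10.8% and 6.0% for change. In round figures these are about 4%, 11% and 26%, and 16%, 11% and 6%.

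**Step 3: cost at n = 30.** Estimating the slope inflates the variance by about 1/26 = 3.8%. Net variance relative to the unadjusted post-training comparison is 0.965 × 1.038 = 1.00 at ρ = 0.3, 0.892 × 1.038 = 0.93 at 0.5, and 0.741 × 1.038 = 0.77 at 0.7. The pilot breaks even at the low end.

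**Step 4: error rates.** In 40,000 simulated null trials with 15 per arm and correlations of 0.3 to 0.7 among those randomised, overall type I error was about 5% for the post-training comparison, the change score and ANCOVA alike. Among trials with a screening imbalance above 0.5 SD it was 8% to 17% for post-training only, 9% to 14% for change, and about 5% for ANCOVA. Selection lowers the correlation, so the post-training excess would be smaller than this in the trial.

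**Step 5: what it means for a definitive trial.** For an illustrative difference of 0.5 SD with 80% power, n per arm = 2 × (1.96 + 0.84)² / 0.5² = 63 unadjusted. Multiplying by 1 − r², with r the correlation among those randomised, gives 58 at r = 0.3 and 48 at r = 0.5. At r = 0.1 it stays at 63.

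**The case against.** The strongest objection concerns where the ANOVA belongs. Section 4.1 assigns it to a definitive trial whose size is not set, so a reader who applies the 15-per-arm imbalance figures to it is relying on the abstract's unrestricted wording. This stands: the figures hold for the pilot only if the abstract governs, and the two places should be reconciled. The proportional variance reduction in Step 2 does not depend on n, provided the definitive trial keeps the same screening step.

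A reader might also infer that the plan discards the screening score or uses it only as an entry gate. The text does not support that. Section 4.1 foresees a score for each assessment task, the abstract includes the baseline task, and the time points are not listed (Figure 2 is not reproduced in the copy reviewed). If screening is the first time point, a group-by-time test already uses it, in effect as a change score. Adjustment still gains 16% to 6% over that.

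A third tempting reading is that the unadjusted comparison is biased. It is not: over allocations it is unbiased, its standard error already allows for chance imbalance, and its type I error is about 5%.

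Finally, covariates are often left to an analysis plan or full protocol, so silence in an article is not in itself an error. That is fair. The point is that the article does choose a method, and a better one is available from data already collected.

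The gain may also lie at the low end. On Days 1 to 4 the co-designed app's assessments use 10/90 to 40/60 mixes of image duration (Table 1), against 50/50 at screening, and they add feedback. This may weaken the correlation in that arm.

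**Conclusion.** The point holds as a recommendation for a better analysis, not as a fault that invalidates the plan. Every randomised participant has one untreated bias score, allocation does not balance it, and the stated ANOVA names no adjustment for it. Under assumed pre-selection correlations of 0.3 to 0.7, adjustment removes about 4% to 26% of post-training variance, or 16% to 6% of change-score variance if screening is already a time point. It also keeps the error rate near 5% after a large chance imbalance. Such an imbalance, above 0.5 SD, occurs in 17% of allocations at 15 per arm and is rare at 50 or more.

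These figures rest on normal scores, equal SDs, selection at zero and correlations that the article does not give. Priority is minor: the pilot's main outcome is recruitment, and its stated conclusion does not depend on the precision of the app comparison.

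**What to change.** In Section 4.1:
- State whether the ANOVA applies to the pilot, the definitive trial or both, and bring the abstract into line.
- List the time points. State that post-training bias scores will be compared between arms with the Day 7 screening score as a covariate (ANCOVA at a named session, or the same covariate in the repeated-measures model) and not as one of the repeated outcomes.
- Compute the screening score by the Section 4.1 formula, since Screening for Eligibility describes the subtraction in the opposite direction.

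The cost is a few sentences and one degree of freedom, with no new data. If the correlation proves low, the gain will be small, and in the pilot close to nil for the post-training score. The pilot can report the observed correlation, which would show how far adjustment reduces the definitive sample size.

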### 4.2. Data Management and Monitoring

In order to protect the confidentiality of the participants and for the data to be de-identified, all the participants will be allocated a unique subject number upon recruitment. All the hard copy questionnaires will contain the unique subject number and no other participant-related identifiers. All the informed consent forms and the completed hard copy questionnaires will be stored in secured, locked cabinets in restricted areas. The electronic data (which comprise mainly reaction times of the participants) will be automatically synchronized to a cloud database in Singapore (Digital Ocean, Singapore). A copy of the electronic data will be downloaded daily onto a local secured computer and stored onto a research network drive. The password of the local computer will be changed frequently. The study team members will code the data and an independent co-investigator will routinely check the data coding for reliability and quality. All the hard copy forms and electronic data will be kept for at least six years following the completion of the study. 

**Adverse Events:** Any adverse events that occur during the conduct of the pilot study will be reported to the Domain Specific Research Board in accordance with the local institutional policy.**Ethics:** The protocol for this study has been approved by the National Healthcare Group Domain Specific Research Board (DSRB Reference Number: 2019/00934). **Expected Results and Conclusions:** This pilot study will provide valuable information about whether the intended processes for the definitive trial would work. This study is of importance, as it will help guide the actual definitive randomised trial. Recruitment and data-analysis is expected to be completed in a duration of 12 months. The results obtained from this study will be disseminated by means of local and international conferences, and by means of peer-reviewed publications.

## Figures and Tables

**Figure 1 ijerph-17-00752-f001:**
[figure not shown]
Overview of Participant Flowchart.

**Figure 2 ijerph-17-00752-f002:**
[figure not shown]
Overview of the data collection time points and tasks to be undertaken.

**Table 1 ijerph-17-00752-t001:** Overview of timings of the images by the days of intervention.

Day of Intervention	Total Number of Trials	Percentage of Image Sets Presenting for 200 Milliseconds	Percentage of Image Sets Presenting for 2000 Milliseconds
Day 1	200	10%	90%
Day 2	200	20%	80%
Day 3	200	30%	70%
Day 4	200	40%	60%
Day 5	200	50%	50%
